Question 1: Does a 16-week walking program with the wearable robotic exoskeleton induce beneficial changes on musculoskeletal, cardiorespiratory, and endocrine-metabolic health; wheelchair-related functional skills and mobility; and psychosocial outcomes? Hypothesis 1: It is hypothesized that beneficial effects observed during the postintervention and retention measurement times will significantly and meaningfully exceed any changes observed during the control and preintervention measurement times (ie, T_0_ [control measurement time] vs T_1_ [preintervention measurement time] vs T_2_ [postintervention measurement time] vs T_3_ [retention measurement time]).Question 2: What personal factors best determine and predict the beneficial effects of the walking program with the wearable robotic exoskeleton? Hypothesis 2: It is hypothesized that the individuals with the highest level of SCI and the longest time since the SCI (ie, possibly the best determinants and predictors) will be those who respond best to the walking program.Question 3: What program attributes best determine and predict the beneficial effects of the walking program with the wearable robotic exoskeleton? Hypothesis 3: It is hypothesized that the total number of steps taken will be the best determinant and predictor of the measured changes.Question 4: What are the participants’ satisfaction levels with the walking program and the wearable robotic exoskeleton itself, and what are the expectations regarding its future use in the context of a home- or community-based adapted physical activity program? Hypothesis 4: It is hypothesized that WU_SCI_ will (1) express high levels of satisfaction with the walking program using the wearable robotic exoskeleton and with the wearable robotic exoskeleton itself and (2) report on how they envision its future in the context of home- or community-based use to shape the development of an adapted physical activity program in the future.

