##### Wheelchair Abilities

Wheelchair abilities are assessed using the following performance-based wheelchair propulsion tests: (1) 20-meter wheelchair propulsion test (natural and maximal speeds), (2) slalom test, and (3) 6-minute manual wheelchair propulsion test [79-82]. The slalom test is used as a surrogate of trunk control since forward reaching distance is a good determinant (*r*=–0.75) [80] and trunk control is known to be the best predictor of multidirectional seated limits of stability during reaching (*R^2^*=0.95) [83]. The *Wheelchair Skills Test Questionnaire version 5.0* [84] is used as well to assess wheelchair abilities. This questionnaire assesses 34 wheelchair mobility and wheelchair-related skills. Each skill is rated on a 4-point self-reported scale: responses to the question *Can you do it?* include 0 (no), 1 (partially), 2 (yes), and 3 (very well). A capacity score is calculated (0%-100%), reflecting the number of skills that can be partially or completely done. Moreover, it assesses how confident—*How confident are you?* 0 (not at all), 1 (partly), 2 (moderately), or 3 (very)—and how often—*How often do you do it?* 0 (never), 1 (occasionally), 2 (usually), or 3 (always)—each skill is performed to calculate confidence and performance scores (0%-100%).

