#### Laboratory Assessments

##### Bone Mineral Density and Architecture

A DXA system (Lunar Prodigy, GE Healthcare) is used to calculate aBMD at the hip, femoral neck, and the first to the fourth lumbar vertebrae [85]. Moreover, T-scores compare the measured aBMD values of each participant against values predicted from a matched reference group for sex, age, and ethnicity and are expressed as the number of SDs (ie, z scores or T-scores depending on age of participant). Measurements of aBMD and z scores or T-scores are directly provided by the system's software.

In addition, a peripheral quantitative computed tomography (pQCT) system (XCT 3000, Stratec Biomedical Systems) is used to characterize the volumetric bone mineral density (vBMD) and the microarchitecture parameters of trabecular and cortical bones at various imaging sites: 66% of the tibia, 25% of the femur, and 66% of the radius. These sites were chosen to maximize muscle circumference in each scan [86]. To minimize site-selection error between measurement times, images are taken using a standardized protocol including scout views with recommended reference lines [86]. As per current recommendations, reported pQCT outcomes will minimally include the following: total trabecular and cortical mineral content; cortical cross-sectional area and thickness; and biomechanical strength indices calculated from density and area (ie, bone strength indices, polar section modulus, and polar strength strain index) [86]. Outcomes are calculated using a validated open source image analysis software package (Fiji distribution of ImageJ) [87,88].

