### Statistics

#### Sample Size Estimation

The sample size estimate was based on a comparison using the variability of the absolute change (ie, mean ±SD) in both body composition and bone mineral density (ie, main outcomes) measured pre- and postintervention in our preliminary study [61] and computed with a computerized sample size calculator [100]. Considering the self-controlled design of the study, a total of 18 participants are required to have an 80% chance of detecting a significant increase at the 5% level in the leg lean body mass (kg) at the tibia measured by DXA from 14.0 to 15.8 ±2 mg/cm^3^ [61]. Likewise, a total of 18 participants are required to have an 80% chance of detecting a significant increase at the 5% level in the bone mineral density (mg/cm^3^) at the tibia measured by pQCT from 466 to 532 ±70 mg/cm^3^ [61]. Considering the dropout rate of 7.1% found during the feasibility study [46], an additional 2 participants were added for a total sample size of 20 participants.

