#### Quantitative and Qualitative Analyses

Descriptive statistics (eg, mean, SD, and 95% confidence interval) will be calculated for data summarizing sociodemographic characteristics as well as clinical and laboratory outcomes collected at the different measurement times. The normality of all data distributions and the absence of outliers will be verified via the Shapiro-Wilk test of normality and the absence of studentized residuals greater than ±3 SDs, respectively. Whenever applicable, the level of significance will be set at *P*≤.05 for all statistical tests and the data will be analyzed using SPSS, version 25.0 (IBM Corp).

For Hypothesis 1, one-way analysis of variance for repeated measures (ie, normally distributed continuous data) or Freidman tests (ie, non-normally distributed continuous or categorical data) with planned comparisons based on the hypothesis and Bonferroni correction will be conducted to detect significant time effects, with a special interest for the preintervention (T_0_ vs T_1_), intervention (T_1_ vs T_2_), and retention (T_2_ vs T_3_) phases. In accordance with the principles of a classic intention-to-treat approach, all participants will be included in the final analyses, regardless of withdrawal, compliance, or unintentional missing data. For missing data, imputation of the mean value for the specific group at the specific assessment time will be used. Per-protocol exploratory analyses will also be performed comparing outcomes for those with walking program compliances of greater than 75% to examine maximum treatment efficacy.

For Hypotheses 2 and 3, Pearson or Spearman correlation coefficients will investigate the strength and direction of the relationships between the overall observed changes ([T_1_–T_2_] / T_1_ × 100) for each personal factor (ie, dependent variable) and the program characteristics (ie, independent variable). Independent variables having reached a critical threshold (*P*≤.25) will then be confronted in a stepwise multiple linear regression analysis to identify the three best predictors for each dependent variable and the coefficient of determination (*R^2^*) of the model. To determine the factors for identifying the best responders to the program, analyses similar to the previous ones will be completed, except that the independent variables will be sociodemographic characteristics, anthropometric parameters, characteristics of the SCI, personal factors, and functional disability.

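### The percent-change response for Hypotheses 2 and 3 scores gains as negative, fails at zero or negative baselines, and is attached to the wrong variables

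*Protocol article*

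**What the plan says.** The protocol article (Quantitative and Qualitative Analyses, paragraph on Hypotheses 2 and 3) fixes the response as "overall observed changes ([T_1_–T_2_] / T_1_ × 100) for each personal factor (ie, dependent variable) and the program characteristics (ie, independent variable"). The coefficients "will investigate the strength and direction of the relationships", so their sign is to be interpreted. Selection follows: "Independent variables having reached a critical threshold (*P*≤.25) will then be confronted in a stepwise multiple linear regression analysis". The formula has no exception by scale and no rule for a zero or negative T1. The same paragraph later lists personal factors among the independent variables when it turns to the best responders.

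Hypothesis 2 (Objectives) predicts that the best responders will be "the individuals with the highest level of SCI and the longest time since the SCI". Hypothesis 3 expects total steps to be the best predictor of change.

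The outcomes are on very different scales. DXA reports areal density with standardised values ("ie, z scores or T-scores depending on age of participant"). The wheelchair skills questionnaire yields a capacity score from 0% to 100% and is also used "to calculate confidence and performance scores (0%-100"%). The Beck inventories rise with worse symptoms (Psychological Health). Ankle dorsiflexion is part of the range-of-motion assessment, and only values at or below -5° are excluded at entry.

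**The concern.** Three faults can be read from the text alone.

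- **Sign.** A higher-is-better outcome that improves gets a negative response, and a lower-is-better outcome that improves gets a positive one. If more steps bring more benefit, r is negative for bone density and lean mass but positive for depression. A table of such coefficients is easily misread.
- **Domain.** At T1 = 0 the ratio does not exist. At negative T1 the same improvement changes sign, and close to zero it becomes very large. On those scales the ordering of participants by response is distorted, and with 20 people one extreme value can dominate a Pearson coefficient.
- **Roles.** The sentence attaches the change to personal factors and calls them dependent. Hypothesis 2 needs them as predictors.

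A fourth matter is only a risk. Dividing by baseline gives larger percentages to people who start low when everyone gains the same amount, so a predictor that tracks baseline could appear to predict response.

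The Discussion says that the characteristics of the best responders will inform clinical decisions or a referral algorithm, so the response measure matters.

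**Working it through.** **Inputs from the article.** Response = (T1 − T2)/T1 × 100. Lean mass: "measured by DXA from 14.0 to 15.8 ±2 mg/cm^3" (read here as kg, since the sentence names kg for the outcome and prints a density unit after the figures). Bone mineral density: "measured by pQCT from 466 to 532 ±70 mg/cm^3". Planned n = 20.

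**Sign.**
- Bone mineral density: (466 − 532)/466 × 100 = −14.2%.
- Lean mass: (14.0 − 15.8)/14.0 × 100 = −12.9%.
- A symptom score falling from 20 to 10 (illustrative): (20 − 10)/20 × 100 = +50%.

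All three are improvements. For one outcome with positive T1, reversing the sign changes the direction of r but leaves |r|, P and R² as they are.

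**Zero and negative baselines.** Take the same improvement of +0.5 in a T-score:
- −2.5 to −2.0: (−2.5 + 2.0)/(−2.5) × 100 = +20%
- 0.5 to 1.0: (0.5 − 1.0)/0.5 × 100 = −100%
- −0.1 to 0.4: (−0.1 − 0.4)/(−0.1) × 100 = +500%

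Dorsiflexion from −4° to 2° gives (−4 − 2)/(−4) × 100 = +150%, although a gain from a positive start gives a negative value. A wheelchair-skill score of 0% at T1 gives no value. The same holds for symptom scores if they are scored from 0, which the article does not state for the Beck inventories.

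**Roles.** Hypothesis 2 has personal factors predicting benefit. The analysis sentence has personal factors as the dependent variable. The end of the same paragraph has personal factors as independent variables. These cannot all stand.

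**Baseline coupling (conditional).** With an equal gain of 1.8 kg for everyone, a person starting at 10 kg gains 1.8/10 = 18% and one starting at 18 kg gains 1.8/18 = 10%.

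Simulation: n = 20, 40,000 runs, baseline 14 ± 2 kg measured without error, and a factor correlated −0.5 with baseline that has no effect of its own on the gain. The correlation, the reading of 2 kg as between-person SD, and the SD of individual change are assumptions. Mean gain is 1.8 kg. Percent change is oriented here so that gain is positive.

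| Additive gain: SD of change (kg) | Mean spurious r | P≤.25 | P<.05 | P<.05, T2 adjusted for T1 |
|---|---|---|---|---|
| 0.3 | 0.32 | 62% | 30% | 5% |
| 0.5 | 0.23 | 46% | 17% | 5% |
| 1.0 | 0.13 | 32% | 9% | 5% |
| 2.0 | 0.06 | 27% | 6% | 5% |

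- Factor-baseline correlation −0.3: P<.05 in 13%, 9%, 6% and 5%.
- Correlation +0.5: the same rates as in the table, with the spurious r reversed.
- Gain proportional to baseline (mean 1.8/14 = 12.9%, SD equal to the same kg values divided by 14), correlation −0.5: percent change stays at 5% throughout, unadjusted T2 − T1 gives 29%, 16%, 8% and 6%, and the baseline-adjusted model stays at 5%.
- Measurement error in T1 (reliability 0.90, assumed): in a separate run the baseline-adjusted model reached up to 8% when the factor correlated 0.5 in size with baseline.

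**The case against.** A reader might infer that the measure builds in support for Hypothesis 2. The article does not support that. Nothing in it says that a higher or longer-standing injury goes with a lower baseline. If the link runs the other way, the bias works against Hypothesis 2. On outcomes where poorer status means a higher value, such as the Beck scores, starting worse means a larger denominator. The gain must also be roughly additive. Under a proportional gain percent change is the unbiased measure and raw change is not.

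The higher rates also need an SD of change far below the article's own figure. Sample Size Estimation says that it used the variability of the absolute change, which points to an SD near 2 kg, where the rate is 6%. This objection stands, and the coupling is only a conditional risk.

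The sign fault can be called notation, since within one outcome with positive T1 it alters neither selection nor fit. That is right, but the plan intends to interpret direction across outcomes that improve in opposite directions.

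The zero and negative cases do not touch the main outcomes, bone mineral density and body composition, which are strictly positive. Areal density is also recorded beside the T-scores. That limits the reach of the fault but leaves the formula unusable on other scales for which no exception is made.

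Finally, Hypothesis 1 and the sample size do not use this ratio. That bears on severity.

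**Conclusion.** The response formula is wrong as written on three counts that need no assumptions. It scores the gains assumed in the sample size as −14.2% and −12.9% while scoring improvement on lower-is-better scales as positive. It is undefined at T1 = 0 and reverses at negative T1 on scales that the article describes. It names personal factors as the dependent variable, against Hypothesis 2 and against the end of its own paragraph.

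The dependence on baseline is a conditional caution. For an assumed factor-baseline correlation of −0.5, an additive gain, baseline 14 ± 2 kg and n = 20, the false-positive rate at P<.05 is about 6% to 30% for an SD of change from 2.0 down to 0.3 kg. It is at the nominal 5% for a proportional gain. The article states neither the link with baseline nor the form of the gain, so no bias towards Hypothesis 2 is shown.

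Severity: should be fixed. The fault is confined to the predictor analyses.

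**What to change.** For each health outcome, regress the T2 value on the T1 value plus the factor of interest. For the factor's coefficient this is the same as modelling T2 − T1 adjusted for T1. Code every outcome so that a positive coefficient means benefit. State that the health outcomes are the dependent variables, with personal factors (Hypothesis 2) and program attributes (Hypothesis 3) as independent variables. If percent change is still wanted, define it as (T2 − T1)/T1 × 100, use it descriptively, and restrict it to strictly positive ratio-scale outcomes. Reversing the sign alone would cure neither the zero and negative baselines nor the dependence on baseline.

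Cost: a change of wording, one degree of freedom per model, and no new data. Some residual bias remains if T1 is measured unreliably (up to 8% against 5% in the check above), and the text should acknowledge it.

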## Methods

### Study Design

A prospective, longitudinal, self-controlled interventional study with multiple discrete measurement times will be used to assess outcomes at baseline (ie, preintervention phase), during the intervention, and thereafter (ie, retention phases) (see Figure 2). While this design may contrast with *classic* study designs frequently recommending a separate comparison group to assess efficacy or effectiveness, the use of a separate comparison group was judged as nonideal in the context of this study, based on the challenges linked to the classification and quantification of the severity of SCIs and their heterogeneous consequences [65]. In addition, interventional trials of new technologies document that potential participants are reluctant to participate, refuse to adhere to the requirements of a control group, or withdraw for the most part from a control group [66,67]. To strike an optimal balance between the need to have a control group with the anticipated strong desire of potential participants to engage in the wearable robotic exoskeleton–assisted walking program, while also considering the amount of, and timeline limits linked to, the study’s funding, the study includes a 4-week observation phase prior to the start of the intervention. Since only individuals with a chronic SCI with *stable* overall health status and life habits will be recruited, outcome measures will be assessed at the start and at the end of the 4-week observation phase. These outcome measures will provide data about each participant’s natural variability and will enable us to detect whether the intervention has an effect greater than the underlying natural variability (ie, patient-specific minimal detectable change criteria computed); they will also enable us to test the effects of the intervention (ie, pre- vs postintervention responses). This boosts the ethical acceptability of the project, minimizes the impacts of potential and unmeasured confounding variables, facilitates recruitment, and mitigates the risk of experimental attrition. Lastly, semistructured interviews and an online questionnaire will capture participants’ satisfaction levels and perspectives about the wearable robotic exoskeleton–assisted walking program and the mobility technology in itself (ie, the wearable robotic exoskeleton).

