
Many stakeholders may benefit from this interventional study. For WU_SCI_ who have no or very limited walking ability, the walking program with the wearable robotic exoskeleton is not expected to have any reversal effect on their walking capacity without this novel mobility assistive technology. However, this project is relevant since it will generate the first evidence of the anticipated cardiorespiratory, musculoskeletal, and endocrine-metabolic health adaptations upon completion of a walking program with a wearable robotic exoskeleton. For the first time, the extent to which these adaptations translate into beneficial effects on functional capacity will also be verified, as will their effects on health-related quality of life and psychological health. This includes the psychological well-being domain, which was not specifically measured during the feasibility study but was mentioned by the majority of participants. Given the fact that the population of WU_SCI_ continues to grow and that they now live longer, these potential beneficial effects are further warranted. The caregiver burden and the potentially costly long-term expenditures associated with adverse health events may also decrease. For rehabilitation professionals, the proposed project is relevant since strengthened evidence regarding the effects of the walking program and the characteristics of the best responders will be generated and will inform clinical decision-making processes or the development of a clinical algorithm for referring individuals with SCIs to a walking program. For rehabilitation program administrators and policy makers, the proposed study is relevant since the evidence generated may further confirm the need for publicly funded clinical and technological infrastructures to create structured programs incorporating walking technologies, such as the wearable robotic exoskeleton, and outcome measures into rehabilitation or adapted physical activity centers. Both program administrators and policy makers will need to work collaboratively and cohesively to develop creative solutions to address this current service gap and engage in transformative improvements. For the research community, this project provides a unique opportunity to create a strong multidisciplinary team of well-established scientists with diverse and complementary academic training as well as clinical and fundamental research expertise. For manufacturers with an interest in wearable robotic exoskeletons, among others, this project is relevant since the input from powered exoskeleton end users (ie, WU_SCI_) will become available and may enrich the continuous quality improvement process. This process is imperative to further support and accelerate the development of wearable robotic exoskeletons and to reach key commercialization milestones for the technology to become personalized and accessible for WU_SCI_ interested in home or community use (ie, neuroprosthesis) in the next decade.

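### The predictor and best-responder analyses use only the T1–T2 percent change and never check whether its spread exceeds the T0–T1 natural variability the study measures

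*Protocol article*

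**What the plan says.** Under Quantitative and Qualitative Analyses, the Hypothesis 2 and 3 analyses are built on "the overall observed changes ([T_1_–T_2_] / T_1_ × 100) for each personal factor (ie, dependent variable"). I read this as the percent change in each outcome, since the outcomes are what change between T1 and T2. Independent variables that pass a P≤.25 screen "will then be confronted in a stepwise multiple linear regression analysis to identify the three best predictors for each dependent variable". The responder analysis reuses the approach with other independent variables: "To determine the factors for identifying the best responders to the program, analyses similar to the previous ones will be completed". No threshold for calling someone a responder is given.

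The control phase is described under Study Design: "the study includes a 4-week observation phase prior to the start of the intervention". Its measurements are there to "detect whether the intervention has an effect greater than the underlying natural variability (ie, patient-specific minimal detectable change criteria computed"). In the analysis section the T0–T1 comparison is named only for Hypothesis 1, "with a special interest for the preintervention (T_0_ vs T_1_), intervention (T_1_ vs T_2_), and retention (T_2_ vs T_3_) phases". The Discussion expects that the "characteristics of the best responders will be generated and will inform clinical decision-making processes".

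**The concern.** In a single-arm study, the spread of individual T1–T2 changes combines true differences in response, within-person fluctuation and measurement error. The last two can be estimated from T0–T1, and the design relies on that phase because it has no comparison group. The analyses that make claims about who benefits do not use it. If everyone gained the same amount, the plan would still report three best predictors and an R² for each outcome, and nothing in the output would show that there was no response variation to predict.

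A second problem lies in the outcome itself. T1 is subtracted in the numerator and divides in the denominator. A factor related to the T1 value can therefore be associated with percent change without being related to response.

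At stake is the intended use of the responder characteristics in clinical decisions and a possible referral algorithm.

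**Working it through.** **Plan's own figure.** The article gives no figure for these analyses. The sample size is 18, plus 7.1% dropout: 18/(1 − 0.071) = 19.4, so 20. I use n = 20.

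**1. How much of the change can be response.** Take change as later minus earlier and assume independent errors with the same variance SEM² at each visit.
- Var(T0–T1 change) = 2·SEM².
- Var(T1–T2 change) = SD²(response) + 2·SEM².
- Hence SD²(response) = SD²(T1–T2) − SD²(T0–T1).
- With k = SD(T1–T2)/SD(T0–T1), the response share is 1 − 1/k².

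| k | share of variance that can be response |
|---|---|
| 1.0 | 0% |
| 1.1 | 17% |
| 1.2 | 31% |
| 1.5 | 56% |

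This is an upper limit if variability over 16 weeks exceeds that over 4 weeks.

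**2. How well k is known at n = 20.** If the two SDs were independent, the 95% factor would be √F(0.975; 19, 19) = 1.59. They are not: T1 error enters the two changes with opposite signs, so under pure noise their correlation is −SEM²/(2·SEM²) = −0.5. The paired-variance interval uses K = 1 + 2(1 − r²)t²/(n − 2) and factor √(K + √(K² − 1)). With r = −0.5 and t(18) = 2.101, K = 1 + 2 × 0.75 × 4.414/18 = 1.368, and the factor is √(1.368 + 0.933) = 1.52. So the observed ratio must be about 1.5 before the interval for response SD excludes zero. By simulation this happens in about 13% of trials at a true k of 1.2 and about 45% at 1.5.

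**3. Noise against the planned gain.** Assume the ±SD in Sample Size Estimation is a between-person SD. Then SEM = SD·√(1 − ICC) and MDC95 = 1.96·√2·SEM. The reliability (ICC) is not in the article, so I show a range.

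| ICC | MDC95, leg lean mass (SD 2; planned gain 1.8) | MDC95, tibia bone density (SD 70; planned gain 66) |
|---|---|---|
| 0.80 | 2.48 | 86.8 |
| 0.90 | 1.75 | 61.4 |
| 0.95 | 1.24 | 43.4 |
| 0.98 | 0.78 | 27.4 |

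At ICC 0.90 or below, one person's noise limit is about as large as the planned mean gain, or larger.

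**4. Factors related to T1.** I simulated the same absolute gain in everyone, with a factor correlated 0.5 with T1. It reached P≤.05 against the percent change in 17% to 26% of trials for ICC 0.80 to 0.98, instead of 5%. With the mean of T0 and T1 as baseline the rate was 12% at ICC 0.80 but 28% at 0.98. Averaging therefore helps where error dominates. It does not help where the denominator drives the association.

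**5. Choice of baseline.** Noise variance of an individual change, in units of SEM²:
- T2 − T1: 1 + 1 = 2.
- T2 − mean(T0, T1): 1 + ½ = 1.5.
- (T2 − T1) − (T1 − T0) = T2 − 2T1 + T0: 1 + 4 + 1 = 6.

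Averaging reduces the noise; subtracting the control-phase change triples it.

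**6. Would T0–T1 serve as a negative control for predictors?** No. I simulated an identical response in everyone and one unrelated factor. Of the factors falsely significant for T1–T2, 88% had the opposite sign in T0–T1, and almost none were significant in the same direction. A rule that rejects only factors predicting both changes alike would pass nearly all of them.

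**The case against.** The strongest reply has four parts.

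*The plan ranks nobody.* It regresses a continuous change, and noise in a dependent variable lowers R² and precision without biasing slopes for factors unrelated to T1 error. This stands. A reader might infer that a person with a chance-low T1 reading is labelled a best responder, or that noise distorts the slopes for lesion level and time since injury. The article supports neither: it sets no individual label, and bias needs a link between the factor and the T1 value.

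*False predictors come mainly from small n and selection.* This also stands. With an identical effect in all 20 participants, the screen plus stepwise entry at P≤.05 (my assumption; the article gives no entry level) selects at least one of 5, 10 or 15 unrelated candidates in about 23%, 42% and 55% of trials, with mean R² of about 0.29 to 0.36 when one is selected. Using the control phase would not remove this.

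*Study Design ties the control phase to the intervention effect, not to predictor models.* It says the data "will enable us to detect whether the intervention has an effect greater than the underlying natural variability", which Hypothesis 1 addresses. A reader might infer a flat contradiction; there is none. How the patient-specific criteria apply to individuals could be set out in an analysis plan that is not shown. But the outcome formula for Hypotheses 2 and 3 is fixed in the article, and it leaves T0 out.

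*The spread check has low power and these are not the main outcomes.* Both are true. They limit how the check may be used, not whether the two SDs should be reported.

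**Conclusion.** The concern holds in limited form. The Hypothesis 2, Hypothesis 3 and best-responder analyses never ask whether the spread of T1–T2 change exceeds the natural variability measured over T0–T1, so observed differences in change may be taken for differences in response. Factors related to the T1 value are biased as well.

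The ceiling on explainable variance runs from 0% to 56% as the SD ratio goes from 1 to 1.5, and at n = 20 that ratio is known only within a factor of about 1.5. For many outcomes the study will be unable to tell response differences from noise, and equally unable to show that response is uniform.

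This rests on independent errors of equal variance at each visit. The MDC figures also rest on an assumed ICC and on reading ±SD as between-person. The Hypothesis 1 conclusions are not affected.

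**What to change.** For every outcome measured at T0, T1 and T2:

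1. Report the SD of the T0–T1 and T1–T2 changes on one scale, and the implied SD of true response with a 95% CI that allows for the shared T1 (paired-variance method or a mixed model).
2. Where that interval includes zero, describe the predictor results as exploratory associations with observed change and claim no identified responders. State that the check has low power at n = 20 and that absence of evidence is not evidence of uniform response.
3. Use the mean of T0 and T1 as the baseline in the predictor analyses, which cuts the noise variance of change from 2 to 1.5 SEM². Note that dividing by baseline can still create associations with factors related to it.
4. Do not subtract the T0–T1 change, and do not clear a predictor because it fails to predict T0–T1 change equally; chance predictors tend to reverse sign there and would pass.

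The cost is extra analysis of data already planned. Some outcomes will carry no responder claim. A 4-week phase may understate 16-week variability. Respiratory gas analysis has no T0 value and cannot be covered. False selection from stepwise modelling at n = 20 remains and needs its own caveat.
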